### Identification, consent and screening of patients

Potential participants aged 18 years or older with CT scan confirmed bronchiectasis, where bronchiectasis is the predominant primary respiratory disease, will be identified and recruited through secondary care NHS sites. Potential participants will be identified by clinicians and members of the research team from patients attending outpatient clinics, spirometry, oxygen services, inpatient admissions and by examination of databases such as local, BronchUK^19^ and EMBARC^20^ registries. Primary care practices may also be set up as Participant Identification Centres (PICs) to identify potential participants and signpost them to an appropriate secondary care recruitment site.

Potential participants will be approached in person or by post with a trial-specific Patient Information Sheet (PIS) (see online supplemental file). Each potential participant will have time to read and consider the PIS before having an opportunity to discuss the trial further with a member of the research team. Written, informed consent using a trial-specific Consent Form (see online supplemental file) will be obtained by a medically qualified member of the research team prior to any trial specific screening activity.

10.1136/bmjopen-2023-071906.supp1Supplementary data

Screening of potential participants will involve:

Collection of demographic data, medical history, medication history and smoking history.Lung function as measured by spirometry.Modified Reiff scoring^21^ of the latest CT scan performed as part of standard care.Quality of life measurements including Quality of Life Bronchiectasis (QoL-B) questionnaire,^22^ St George’s Respiratory Questionnaire (SGRQ)^4^ and the 5-level EuroQol5D index (EQ-5D-5L) questionnaire.^23^BSI score.^11^Assessments of breathlessness including the Medical Research Council Dyspnoea (MRCD) Score^24^ and Baseline Dyspnoea Index (BDI) and Transition Dyspnoea Index (TDI), respectively.^25^Health Economics questionnaires.Baseline bloods (full blood count including differentials).

All participants of childbearing must be willing to use an acceptable form of contraception (as listed in the PIS) throughout the trial from the date of consent until 7 days after their last dose of trial medication. Additionally, women of childbearing potential will be required to have a negative urine pregnancy test at baseline/screening to be eligible for the trial.

### Randomisation

Patients who are confirmed as eligible will be randomised to one of three treatment arms dual therapy (LABA+LAMA), triple therapy (LABA+LAMA+ICS) or matched placebo, in a 2:2:1 ratio (respectively). Randomisation is carried out by appropriately delegated members of the research team using random permuted blocks of variable length within strata via the Sealed Envelope system; a central, secure, 24-hour web-based randomisation system with concealed allocation.

Randomisation is stratified by two variables: BSI score (BSI score of 0–8 or 9+) and by baseline ICS drug therapy (ICS user or non-ICS user at baseline).

### Intervention

Treatment allocation is double-blind, each inhaler is identical in appearance to maintain the blind. Participants will have a dose of one inhalation of their trial inhaler per day, it is advised that the dose is taken at the same time of day wherever possible, for the 12 month (365 days) trial period. Dose modifications are not permitted.

The contents of each inhaler are described in table 2.

**Table 2 T2:** Inhaler contents

Inhaler	Contents of each dose delivered	Name of equivalent commercially available product
Dual therapy (LAMA/LABA)	55 µg umeclidinium 22 µg vilanterol	Anoro Ellipta dry powder inhaler
Triple therapy (ICS/LAMA/LABA)	92 µg fluticasone furoate 55 µg umeclidinium 22 µg vilanterol	Trelegy Ellipta dry powder inhaler
Placebo	Placebo	Matched placebo dry powder inhaler

ICS, inhaled corticosteroid; LABA, long acting beta agonist; LAMA, long acting muscarinic antagonist.

Each inhaler contains 30 doses of medication. Due to the shelf life of the labelled inhalers, they will be shipped to participants approximately monthly throughout their participation in the trial. Confirmation of receipt of trial medication will be carried out by a member of the research staff telephoning the patient following each trial medication shipment. Trial inhalers are returned by participants at the end of their involvement in the trial and compliance monitored.

### Follow-up visits and participant assessments

Follow-up visits will take place at the local trial site at 1, 6 and 12 months with assessments performed as detailed in table 3.

**Table 3 T3:** Schedule of events

Assessment/activity	Visit 1	Visit 2	Telephone call to participant	Visit 3	Telephone call to participant	Visit 4	Telephone call to participant	24 months follow-up
	Screening/baseline	1 month follow-up		6 month follow-up		12 month follow-up		
	Day 0	1 month (−1/+2 weeks)	3 days (±1 day) following dispensing 2 to 6/7	6 months (−1/+2 weeks)	3 days (±1 day) following dispensing 6/7 to 13	12 months (+2 weeks)	7 days after last dose of IMP (+3 days)	
Written informed consent	X							
Demographics	X							
Contact details (participant telephone number and address)	X	X	X	X	X			
Medical history	X							
Medication history	X							
Smoking history	X	X		X		X		
Spirometry including % predicted (FEV_1_ and FVC)	X	X		X		X		
Bronchiectasis Severity Index calculation	X					X		
Modified Reiff scoring of prior CT scan	X							
St George’s Respiratory Questionnaire (SGRQ)	X	X		X		X		
Quality of Life- Bronchiectasis (QoL-B)	X	X		X		X		
Breathlessness: Baseline and Transition Dyspnoea Indices (BDI and TDI)	X	X		X		X		
MRC Dyspnoea Score	X	X		X		X		
Healthcare Utilisation Questionnaire	X	X		X		X		
Time and Travel Questionnaire						X		
Quality of life EQ-5D-5L	X	X		X		X		
Baseline blood test (FBC with differentials)	X							
Pregnancy test (urine, females of childbearing potential)	X							
Contraception discussion	X							
GP results request/ prior eosinophil levels extracted from medical records/primary care data sets	X							
Eligibility confirmation	X							
Randomisation	X							
Stop prerandomisation inhalers with the exception of short acting beta-agonist (SABA) and commence trial inhalers	X							
Trial inhaler delivered to participant on site at face-to-face visit	X							
Trial inhaler delivered to participant by post (2–4 days prior to each telephone call)			X	X	X			
Confirmation of trial inhaler receipt			X	X	X			
Inhaler technique	X	X		X				
Concomitant medication		X		X		X		
Issue Patient Exacerbation Diary	X							
Participant exacerbation diary review (or reminder to use at telephone calls)		X	X	X	X	X		
Compliance check and documentation (count of returned trial inhalers and dose counts)		X		X		X		
Number of hospital admissions for bronchiectasis exacerbation		X		X		X		X
Number of emergency hospital admissions		X		X		X		X
Adverse event reporting		X	X	X	X	X	X	
Review of primary care records						X		
Mortality data								X

EQ-5D-5L, 5-level EuroQol5D index; FEV_1_, forced expiratory volume in 1 s; FVC, forced vital capacity; GP, general practitioner.

Participants will be required to complete an Exacerbation Diary weekly throughout their 12 month participation in the trial. In this diary, participants will record whether or not they have experienced any exacerbations during the week and any steps or treatment taken for the exacerbation. This will be reviewed by a member of the research team at each trial visit and collected at the final 12 month follow-up.

Long term follow-up will be carried out 24 months after the screening/baseline visit for participants who reach this time point within the lifetime of the trial. Data collected at this time point are mortality data, the number of emergency hospital admissions and the number of emergency hospital admissions with exacerbations of bronchiectasis. Participants will not be contacted for this follow-up, instead data will be collected from sources such as patient medical records, BronchUK^19^ and/or EMBARC^20^ registries or routinely collected Hospital Episode Statistics (HES) and Office of National Statistics (ONS) data.

At the end of their trial participation, participants will stop taking trial medication and continue to have their condition managed through the standard care pathway.

### Pharmacovigilance

All AEs will be recorded in both the participant’s medical records and on the electronic Case Report Forms (eCRF) within the trial database. AEs that are judged by an investigator as consistent with the usual clinical pattern for patients with bronchiectasis (such as cough, increased sputum volume and/or consistency, change in sputum colour, wheeze, breathlessness, fatigue and haemoptysis) are not reportable AEs. AEs meeting the seriousness criteria (serious adverse events) will be reported within 24 hours of awareness. Suspected Unexpected Serious Adverse Reactions (SUSAR) will be reported to the MHRA (Medicines and Healthcare products Regulatory Agency) and REC (Research Ethics Committee) within the required regulatory reporting timelines.

Emergency unblinding is available for valid medical or safety reasons where it is necessary for the treating clinician to know which treatment the participant has been receiving. Emergency unblinding should be carried out by the site Principal Investigator or another delegated medically qualified member of the research team by accessing the 24-hour web-based randomisation system.

### Discontinuation and withdrawal

Participants are free to discontinue trial treatment or withdraw from the trial at any time without detriment to their care. Participants choosing to discontinue trial treatment will be invited to complete all trial follow-up visits and assessments. Participants choosing to withdraw from the trial will not take part in any further trial activity. Data collected up to the point of withdrawal will be retained and included in analysis. Participants withdrawn from the trial after they have been randomised will not be replaced.

### Data management

Participant data will be entered by delegated site staff into the trial-specific Clinical Data Management System (CDMS) using Sealed Envelope’s Red Pill (Sealed Envelope, London, UK). CDMS users have password limited access restricted to own role and site as appropriate to their delegated duties. Each potential participant will be assigned a unique sequential screening number by site staff, this unique identifier is used to add the participant to the CDMS and becomes their participant ID at the time of randomisation. Overall responsibility for data collection, quality and retention lies with the Chief Investigator who will also hold the final trial data set. Data will be handled, computerised, stored and archived in accordance with the General Data Protection Regulation (2018), and the latest Directive on GCP (2005/28/EC). Newcastle Clinical Trials Unit (NCTU) staff monitor trial conduct and data integrity in accordance with the trial Monitoring Plan. The trial-specific Data Management Plan (DMP) and Data Validation Plan (DVP) include details on how data will be managed and validated throughout the trial.

### Analysis

#### Analysis of the primary outcome measure

The primary outcome—number of bronchiectasis exacerbations per participant requiring antibiotics over 12 months—will be compared between randomised groups using negative binomial regression adjusted for stratification factors. This model will be used to compute CIs to test the superiority and non-inferiority hypotheses. The two-sided 95% CI for difference in mean number of exacerbations per year between the combination of LAMA/LABA and ICS/LAMA/LABA compared with placebo will be found: the placebo versus LAMA/LABA hypothesis will be rejected if the upper limit is lower than 0. We will estimate the difference between LAMA/LABA and ICS/LAMA/LABA arms on the relative scale using the incidence rate ratio, and test whether the upper boundary of the two-sided 90% CI is lower than 1.2. We will consider the time at risk to be the time not spent in exacerbation (so that while a patient is in an exacerbation, they are not included as at risk for another).

A secondary analysis will define the at-risk time as the entire length of follow-up for the patient. Estimates will then be adjusted for sites, the stratification factors and other baseline covariates that are known to be strongly related to outcome (eg, age, smoking, bronchiectasis hospitalisations in year prior to trial—these will be prespecified in the Statistical Analysis Plan (SAP)).

We will undertake a sensitivity analysis by excluding those participants who have died. If there is any indication of a differential effect on deaths by treatment, we may consider models that allow the censoring to be informative. For participants who are lost to follow-up by 12 months, their information will be included in the statistical models up to the point that they are lost to follow-up. If loss to follow-up is higher than 10% we will conduct sensitivity analyses to investigate the impact.

We will also explore time to first exacerbation using a Cox regression, and a recurrent events analysis to allow for subsequent exacerbations. In addition, we will use mortality and hospitalisations due to bronchiectasis exacerbation data collected up until 24 months to extend the modelling beyond 12 months as a sensitivity analysis.

For the primary superiority hypothesis, statistical analyses will be according to the intention to treat principle with a per protocol analysis performed as a sensitivity analysis. The per protocol analysis will exclude participants who were not compliant (at less than 75%) with their trial medication or who had a major protocol violation (to be pre-specified in the SAP).

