### Sample size calculations

The original sample size calculation was based on the number of exacerbations among a similar population in prior national audits.^15 23^ The average number of exacerbations was 2.3 per year. Restricting trial entry to those who had ≥3, the original inclusion criteria (assuming a Poisson distribution) gives an average of around 3.8. We therefore assumed, given Hawthorne effect and regression to the mean, that the placebo arm would have a lower mean exacerbation rate than this, and assumed a mean of 2.4 over 1 year. The sample size was chosen so that the trial was well powered to detect a clinically meaningful fall in mean exacerbation rates for bronchiectasis exacerbations to 1.9 year in LAMA/LABA and ICS/LAMA/LABA arms (approximately 20% reduction). This effect size is realistic when compared with the 20%–30% reduction seen in COPD trials with dual bronchodilators/triple therapy and is accepted as clinically meaningful. Although likely studying a different sub population in bronchiectasis, a recent inhaled antibiotic trial in bronchiectasis reduced exacerbations by 39%.^4^

For 90% power (two-sided 5% significance level) to conclude that LAMA/LABA is more effective than placebo with the above parameters, we have calculated (assuming large-sample approximation of the Poisson distribution) that a sample size of 600 participants is needed, randomised 240:240:120 between LAMA/LABA, ICS/LAMA/LABA and placebo. This allows for a 5% loss to follow-up. This represents a conservative retention rate compared with over 95% observed in the NIHR *HTA* TWICS study with similar pragmatic design and limited patient burden. This calculation assumes a difference between placebo and LABA/LAMA of 0.5 exacerbations per year (21% relative reduction).

If superiority of LAMA/LABA versus placebo is concluded, we will then test non-inferiority of LAMA/LABA against ICS/LAMA/LABA. The sample size will give 90% power (one-sided 5% type I error) with a 0.38 non-inferiority margin (reflecting 20% of the assumed LAMA/LABA rate).

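### The superiority interval pools both active arms against placebo but is used to conclude that LAMA/LABA alone beats placebo, and the stated superiority power fits the pooled contrast too

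*Protocol article*

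**What the plan says.** In the protocol article, *Analysis of the primary outcome measure* fits a negative binomial model and takes a two-sided 95% interval for the "difference in mean number of exacerbations per year between the combination of LAMA/LABA and ICS/LAMA/LABA compared with placebo". The same sentence then gives the decision rule: "the placebo versus LAMA/LABA hypothesis will be rejected if the upper limit is lower than 0".

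*Sample size calculations* treats LAMA/LABA as one arm of three. Power is given as "For 90% power (two-sided 5% significance level) to conclude that LAMA/LABA is more effective than placebo with the above parameters", with allocation "randomised 240:240:120 between LAMA/LABA, ICS/LAMA/LABA and placebo", and the assumed 0.5 difference is described as placebo against LABA/LAMA. The second step follows from the first: "If superiority of LAMA/LABA versus placebo is concluded, we will then test non-inferiority of LAMA/LABA against ICS/LAMA/LABA".

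Table 4 reports superiority power of 89.8% for rates 2.4 v 1.9, 95.8% for 1.9 v 1.4 and 83.4% for 1.9 v 1.5. The primary objective under *Objectives and outcomes* is looser. It compares dual bronchodilators, given either alone or with ICS, with placebo.

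**The concern.** An interval for the average of the two active arms against placebo does not test LAMA/LABA against placebo, because half of the active-arm weight comes from triple therapy. The pooled result carries over to dual therapy only if adding ICS makes no difference, and that is the question the trial's second test addresses. The introduction does not allow equality to be assumed: it reports fewer COPD exacerbations with ICS, but no clear benefit in earlier bronchiectasis studies.

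At stake is the trial's first primary conclusion. If triple therapy works and dual therapy does not, the stated rule can credit dual therapy with an effect it does not have. It would also open the non-inferiority test without the superiority that the sample size section requires.

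**Working it through.** **Inputs.** Allocation 240:240:120; with 5% loss, 228:228:114 (*Sample size calculations*, "This allows for a 5% loss to follow-up"). Original placebo rate: "assumed a mean of 2.4 over 1 year", active arms 1.9. Updated placebo rate 1.9, active arms 1.4 or 1.5 (Table 4). Two-sided 5%. Method: "assuming large-sample approximation of the Poisson distribution". Negative binomial dispersion is not given; I take k = 0 (Poisson) and k = 0.5 as an assumption.

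**1. The plan's superiority power.** Power = Φ(d/SE − 1.96), with SE = √(λ0/n0 + λ1/n1). For 2.4 v 1.9, d = 0.5:

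- Pooled, 480:120: SE = √(2.4/120 + 1.9/480) = 0.1548; d/SE = 3.230; power **89.8%**, as in Table 4.
- Pooled, 456:114: SE = 0.1588; power 88.3%.
- LAMA/LABA alone, 240:120: SE = √(2.4/120 + 1.9/240) = 0.1671; d/SE = 2.993; power **84.9%**.
- LAMA/LABA alone, 228:114: SE = 0.1714; d/SE = 2.917; power **83.1%**.

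Other pairwise formulas (score, null variance, log rate ratio, square root) reach at most 87.5%. The exact pooled match is without the 5% loss. The non-inferiority figures, by contrast, reproduce with 228 per arm: √(2 × 1.9/228) = 0.1291, and Φ(0.38/0.1291 − 1.645) = 90.3%.

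All three rows, by the same Wald formula:

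| Rates | Table 4 | Pooled 480:120 | LAMA/LABA alone 240:120 | LAMA/LABA alone 228:114 |
|---|---|---|---|---|
| 2.4 v 1.9 | 89.8% | 89.8% | 84.9% | 83.1% |
| 1.9 v 1.4 | 95.8% | 95.5% | 92.5% | 91.2% |
| 1.9 v 1.5 | 83.4% | 82.8% | 76.8% | 74.7% |

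Rows 2 and 3 match the pooled contrast closely, not exactly.

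**2. False claims about dual therapy.** Set dual = placebo = 1.9 and triple = 1.5, with 228/228/114.

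- Pooled difference = 1.9 − (1.9 + 1.5)/2 = 0.20.
- SE = √(V0/114 + 0.25(Vd + Vt)/228), with V = λ + kλ².
- k = 0: SE = 0.1428; Φ(0.20/0.1428 − 1.96) = **29%** (simulation about 28%).
- k = 0.5: SE = 0.1986; Φ(0.20/0.1986 − 1.96) = **17%** (simulation about 15%).
- Intended, with a pairwise interval: 2.5%.

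**3. What happens at the second step.** In a Poisson simulation of the same setting, with the plan's rule (upper 90% limit of the rate ratio below 1.2), the pooled test and non-inferiority both succeed in about 0.25% of trials. With triple at 1.7 this is about 2.4%.

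**4. One data set, two answers.** Observed rates of 2.4 (placebo), 2.2 (dual) and 1.8 (triple), with 228/228/114, Poisson:

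- Pooled: −0.40 + 1.96 × 0.1595 = **−0.09**, so LAMA/LABA superiority is declared.
- Pairwise: −0.20 + 1.96 × 0.1752 = **+0.14**, so it is not shown.

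**The case against.** The best defence is that pooling was intended. The primary objective covers LAMA/LABA with or without ICS, and Table 4's first row is the pooled figure. On that reading the contrast is right and only the hypothesis label is loose. Part of this stands: the documents leave room for a pooled primary contrast, so renaming the hypothesis is a legitimate repair. It does not remove the contradiction. The sample size section names LAMA/LABA as the treatment concluded on and then compares it with ICS/LAMA/LABA as a separate arm.

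The second defence is that non-inferiority would catch the error. For the two-step claim it largely does, as the 0.25% and 2.4% show. A reader might infer that the whole testing sequence is badly inflated, and the documents do not support that. But superiority is concluded first and stands alone whatever the second test shows.

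A reader might also take the wording of the sample size section to mean that the trial was sized on 240 v 120. The arithmetic does not support that, since no pairwise formula tried gives 89.8%. Finally, triple therapy working while dual therapy does nothing is one scenario among several. I kept the triple rate at the plan's own 1.5 and did not use larger effects.

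**Conclusion.** The point holds as a mismatch between contrast and hypothesis that runs through both the analysis and the power. The stated rule can give a wrong primary conclusion: about 29% false claims that LAMA/LABA beats placebo under Poisson counts, or 17% at the assumed dispersion of 0.5, against 2.5% intended. These figures rest on dual = placebo = 1.9, triple = 1.5, 5% loss and a normal approximation. The uncontrolled error is confined to that stand-alone claim. Separately, the 90% power stated for LAMA/LABA against placebo is about 83% to 85% on the plan's own Poisson assumptions. That pooling was the working design is an inference from Table 4; the document does not say so.

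**What to change.** Decide the LAMA/LABA-versus-placebo hypothesis, and open the non-inferiority test, with the two-sided 95% interval for LAMA/LABA minus placebo from the same three-arm negative binomial model. Report triple versus placebo and pooled active versus placebo as separately labelled estimates.

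If the pooled test is to remain primary, name its hypothesis as pooled active versus placebo and require the pairwise interval before any claim about dual therapy.

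In either case, bring *Objectives and outcomes*, the primary analysis section, *Sample size calculations* and Table 4 into line. Restate the LAMA/LABA-versus-placebo power as about 83–85% (2.4 v 1.9), 91–93% (1.9 v 1.4) and 75–77% (1.9 v 1.5), the lower figure with 5% loss and the higher without.

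The analysis change needs no new data, because the model already yields the pairwise interval. The cost is a less favourable stated power, most visibly 75–77% in place of 83.4% in the last scenario. The sample size need not change; *Trial status* reports that recruitment closed on 21 October 2022.

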In the early stages of the trial, it was found that exacerbation rates in prebaseline periods were lower than they had been historically, mostly due to the presumed effect of COVID-19 restrictions. The inclusion criteria were therefore updated in protocol V.5.0 (see Amendments). A recalculation of the power of the trial was conducted assuming that there would be lower exacerbation rates in the follow-up period. We assumed that the placebo exacerbation rate would be an average of 1.9 per year. We recalculated the power for two scenarios: (1) assuming that the same absolute difference (0.5) between LAMA/LABA versus placebo and the same non-inferiority margin (0.38) as previously; (2) the same relative difference (21%) between LAMA/LABA vs placebo and relative non-inferiority margin (20%) as before. Table 4 shows the power of the trial to conclude non-inferiority and superiority.

**Table 4 T4:** Power calculations

Scenario	Mean exacerbation rate			NI margin (relative to active control)	Power*	
	Placebo	ICS/LAMA/LABA (intervention)	LAMA/LABA (active control)		Non-inferiority (%)	Superiority (%)
Presented in original grant application	2.4	1.9	1.9	0.38 (20%)	90.3	89.8
Updated inclusion criteria (same absolute differences)	1.9	1.4	1.4	0.38 (26.7%)	96.3	95.8
Updated inclusion criteria (same relative differences)	1.9	1.5	1.5	0.3 (20%)	83.4	83.4

*Note this is assuming analytical formulae, with simulations giving consistent but slightly higher powers.

ICS, inhaled corticosteroid; LABA, long acting beta agonist; LAMA, long acting muscarinic antagonist; NI, non-inferiority.

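### Non-inferiority is tested as a rate ratio below 1.2, but the stated power (90.3%, 96.3%, 83.4%) was computed for an absolute difference and is too high for the planned test in every scenario

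*Protocol article*

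**What the plan says.** The Protocol article, Analysis of the primary outcome measure, compares the groups by "negative binomial regression adjusted for stratification factors". For dual (LAMA/LABA) versus triple (ICS/LAMA/LABA) therapy, the effect is estimated "on the relative scale using the incidence rate ratio", and the plan is to "test whether the upper boundary of the two-sided 90% CI is lower than 1.2".

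The Sample size calculations section works on another scale: "The sample size will give 90% power (one-sided 5% type I error) with a 0.38 non-inferiority margin", the margin being described as "reflecting 20% of the assumed LAMA/LABA rate". The power formula is introduced as "assuming large-sample approximation of the Poisson distribution". After the change in eligibility, power was recalculated for two scenarios. The first keeps "the same absolute difference (0.5) between LAMA/LABA versus placebo and the same non-inferiority margin (0.38) as previously". The second keeps the relative quantities, with 20% of 1.5 entered as 0.3. Table 4 prints non-inferiority power of 90.3% (active-arm rate 1.9, margin 0.38), 96.3% (rate 1.4, margin 0.38) and 83.4% (rate 1.5, margin 0.3).

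**The concern.** The article fixes both the test and its power, and the two do not match. A margin in events per year and a margin on the rate ratio agree only at one assumed rate. Even at that rate, a test on the difference and a test on the log ratio do not have the same power. The two margins also respond in opposite ways when the event rate falls. A fixed absolute margin becomes easier to meet, because the Poisson variance shrinks. A fixed ratio margin becomes harder to meet, because there are fewer events.

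This bears directly on the amendment. Table 4 is the article's evidence that relaxing the entry criteria, with lower expected rates, left the trial adequately powered. If its non-inferiority column belongs to another test, a reader is misled about the size of the power and, in the second row, about the direction in which it moved. Non-inferiority is a formal step once superiority is shown, so its power matters for interpreting an inconclusive result.

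**Working it through.** **Inputs, all from the Protocol article**

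- Active arms: 240 each, 5% loss to follow-up, so 240 × 0.95 = 228 evaluable per arm (Sample size calculations).
- Active-arm rates: 1.9, 1.4 and 1.5 per year, equal in the two active arms (Table 4). Follow-up is 12 months.
- One-sided 5% type I error, equivalent to a two-sided 90% interval: z = 1.645.
- Poisson variance, as the sample size section assumes.
- Planned margin: rate ratio 1.2, ln 1.2 = 0.1823 (Analysis of the primary outcome measure).

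**Step 1: reproduce the printed figures.** For a difference in Poisson means with a true difference of zero,

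power = Φ( margin / √(2 × rate / 228) − 1.645 )

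- Rate 1.9, margin 0.38: 0.38 / 0.1291 = 2.943; Φ(1.298) = 90.3%.
- Rate 1.4, margin 0.38: 0.38 / 0.1108 = 3.429; Φ(1.784) = 96.3%.
- Rate 1.5, margin 0.30: 0.30 / 0.1147 = 2.615; Φ(0.970) = 83.4%.

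All three match Table 4 to the decimal. The printed powers are therefore difference-scale Poisson powers.

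**Step 2: power of the planned test.** On the log rate ratio the standard error is √(2 / (228 × rate)), so

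power = Φ( 0.1823 / √(2 / (228 × rate)) − 1.645 )

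| Rate | Standard error | Power, ratio < 1.2 | Stated | Shortfall (points) |
|---|---|---|---|---|
| 1.9 | 0.0679 | 85.0% | 90.3% | 5.3 |
| 1.4 | 0.0792 | 74.5% | 96.3% | 21.8 |
| 1.5 | 0.0765 | 77.0% | 83.4% | 6.4 |

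Poisson simulation of the ratio test (400,000 runs per row) gives 84.9%, 74.4% and 77.0%.

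**Step 3: where the gap comes from.** In rows 1 and 3 the margin equals a ratio of 1.2 at the assumed rate (0.38/1.9 = 0.3/1.5 = 0.20), so only the scale differs. In row 2 the margin differs too: 1 + 0.38/1.4 = 1.27. Testing a ratio of 1.27 on the log scale would give 91.8%. Moving from 1.27 to the planned 1.2 brings it to 74.5%. Even on the difference scale, a 20% margin at that rate (0.28) gives 81.1%. Table 4 prints row 2's relative margin as 26.7%, whereas 0.38/1.4 = 27.1%; this may be rounding of the rate and is not material.

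**Step 4: sensitivity.**

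- No dropout (240 per arm): the ratio test gives 86.6%, 76.4% and 78.9%, still below every stated figure.
- For 90% power the ratio test would need 272, 369 and 344 evaluable per active arm. With 5% loss and 2:2:1 allocation, that is about 718, 973 and 908 in total, against 600.
- Overdispersion: the article gives no value. Assuming a negative binomial dispersion k of 0.2 to 1.0, the variance of the log ratio becomes 2 × (1/rate + k) / 228. Power then falls to 74–47%, 65–44% and 67–45% in the three rows.

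**The case against.** The strongest reply has four parts.

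- **The margin is the same in two rows.** The article derives 0.38 as 20% of the assumed rate, and Table 4 labels rows 1 and 3 as 20%. At those rates the margin is a ratio of 1.2, and what remains is the scale of a large-sample approximation. This is correct and explains why the loss there is only 5 to 6 points. It does not restore the printed figures, because the interval will be built on the ratio.
- **Row 2 is an open what-if.** Its relative margin is printed, and the 20% scenario stands beside it. That is fair as far as disclosure goes. But the row is presented as power of the trial under the updated criteria, and nothing tells the reader that the planned test never uses that margin. The contrast between the two updated rows should also not be overdrawn: on the ratio scale they differ by only 2.5 points (74.5% against 77.0%).
- **The Table 4 footnote.** It reports that simulations agreed with the formulae and were slightly higher. Poisson simulation of the ratio test is clearly lower in every row, so the footnote cannot describe that test.
- **Consequences are limited.** Recruitment closed on 21 October 2022, and the decision rule in the analysis section is unambiguous. Restating power changes neither the estimate nor the type I error. This stands, and it limits the remedy to a correction of what is claimed.

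It is also fair that Poisson figures do not fully match the planned negative binomial model. The recalculated powers are therefore best read as values before overdispersion.

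**Conclusion.** The concern holds. The stated non-inferiority powers are arithmetically sound for a difference-scale test, but the planned test is a rate ratio below 1.2. For that test, with 228 per arm, equal true rates and Poisson counts, power is 85.0%, 74.5% and 77.0% rather than 90.3%, 96.3% and 83.4%. At the updated rates it is about 74–77%, not 83–96%. The scenario printed as the strongest is the weakest of the three. These are upper values in one respect: any overdispersion reduces them, by an amount the article does not allow one to fix.

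**What to change.** Before analysis, confirm the rate ratio of 1.2 in Analysis of the primary outcome measure as the single non-inferiority margin. In Sample size calculations, remove the scenario that carries 0.38 to a rate of 1.4. Restate the 90% claim and the non-inferiority column of Table 4 for the log rate ratio test: 85%, 75% and 77%, marked as Poisson values before overdispersion. Adding power under a stated range of dispersion would bring the table into line with the negative binomial model. The footnote on simulations should say which test was simulated, or be dropped.

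The cost is a correction of text and one table. No data collection or decision rule changes. The stated power becomes less favourable, and with recruitment closed it cannot be recovered by enlarging the sample.
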